## Abstract

**Background:**

Whole-genome sequencing (WGS) and whole-transcriptome sequencing (WTS), with the ability to provide comprehensive genomic information, have become the focal point of research interest as novel techniques that can support precision diagnostics in routine clinical care of patients with various cancer types, including hematological malignancies. This national multi-center study, led by Genomic Medicine Sweden, aims to evaluate whether combined application of WGS and WTS (WGTS) is technically feasible and can be implemented as an efficient diagnostic tool in patients with acute lymphoblastic leukemia (ALL) and acute myeloid leukemia (AML). In addition to clinical impact assessment, a health-economic evaluation of such strategy will be performed.

**Methods and Analysis:**

The study comprises four phases (i.e., retrospective, prospective, real-time validation, and follow-up) including approximately 700 adult and pediatric Swedish AML and ALL patients. Results of WGS for tumor (90×) and normal/germline (30×) samples as well as WTS for tumors only will be compared to current standard of care diagnostics. Primary study endpoints are diagnostic efficiency and improved diagnostic yield. Secondary endpoints are technical and clinical feasibility for routine implementation, clinical utility, and health-economic impact.

**Discussion:**

Data from this national multi-center study will be used to evaluate clinical performance of the integrated WGTS diagnostic workflow compared with standard of care. The study will also elucidate clinical and health-economic impacts of a combined WGTS strategy when implemented in routine clinical care.

**Clinical Trial Registration:**

[https://doi.org/10.1186/ISRCTN66987142], identifier [ISRCTN66987142].

## Introduction

Genomic evaluation is emerging as an integral component of the diagnostic workup to facilitate diagnostic classification, risk stratification, and therapy selection in various cancers including hematological malignancies (1). To identify genetic variants that are associated with each type and subtype of hematologic cancer, such as single-nucleotide variants (SNVs), insertions and deletions (indels), oncogenic fusions, larger structural variations (SVs), and copy-number aberrations (CNAs), current standard of care (SoC) employs various, often laborious genetic techniques, including chromosome banding analysis, fluorescence *in situ* hybridization (FISH), genomic arrays, targeted next-generation sequencing (NGS), and reverse transcription polymerase chain reaction (RT-PCR). Although these methods provide clinically relevant information for individual patients, their detection/diagnostic capacities are hindered by low resolution, limited genomic coverage, and/or inability to identify novel genetic alterations, as well as the time and cost associated with performing multiple tests of the same sample. These challenges could potentially be overcome by using whole-genome sequencing (WGS), which covers the entire genome and thereby is capable of providing the most unbiased and comprehensive genetic information (2–5). Similarly, whole-transcriptome sequencing (WTS) that analyzes sequences of all expressed genes and has the ability to detect gene fusions (2, 6) is a method that may improve disease subclassification (6–9). Both WGS and WTS have so far been used primarily as research tools in hematological malignancies but are gaining interest as novel techniques to support diagnosis, prognosis, and therapy selection in a clinical setting (3–5).

Acute lymphoblastic (ALL) and acute myeloid leukemias (AML) are associated with clinically relevant SNVs, CNAs, and SVs including gene fusions (10). Since information on specific genetic aberrations today has a major impact on risk stratification and clinical management in both adult and pediatric acute leukemia, comprehensive genomic profiling by WGS and WTS is expected to be highly informative. Yet, studies that assess their clinical utility and health-economic impact compared to SoC diagnostics are limited.

The potential of a multi-modal sequencing approach as a clinical test was first evaluated in pediatric patients with various types of hematological malignancies and solid tumors at St. Jude Children’s Research Hospital (11). This study showed that the addition of WGS (30×) to combined whole-exome sequencing (100×)/WTS increased the sensitivity (from 78 to 98%) to identify pathogenic variants known from diagnostic testing (5). Using this diagnostic strategy, potentially actionable targets could also be identified that may facilitate future therapy selection and reduce treatment-related toxicities (12). Similarly, a study in myeloid cancers showed that, compared with conventional cytogenetics, tumor-only WGS (60×) analysis performed equivalently or better in identifying clinically relevant genetic variants and also changed risk stratification in a proportion (16%) of the patients (13). Together, these studies highlight the potential benefits of comprehensive precision diagnostic testing when used in routine practice, both to replace current SoC testing and to provide additional information beyond SoC. To advance clinical implementation of WGS and WTS, more studies that assess diagnostic efficiency/utility and health-economic impact of these methodologies are necessary.

## Aim

The aim of this national multi-center study performed by Genomic Medicine Sweden (GMS), in close collaboration with the Clinical Genomics Platform at Science for Life Laboratory (SciLifeLab), is to evaluate whether application of WGS and WTS combined, collectively termed WGTS, is technically feasible and can be implemented as an efficient clinical tool with a high diagnostic accuracy in patients with ALL and AML. Specifically, the combined workflow of WGTS will be compared with current SoC methodologies to identify potential benefits and challenges of WGTS implementation in a routine diagnostic setting. This study will also address whether WGTS will improve the diagnostic yield and patient management as well as if these assays combined are cost-effective. The ultimate goal of this study is to evaluate if WGTS can replace current diagnostic SoC methods of patients with ALL and AML across Sweden. This manuscript outlines the conceptual and experimental designs for the study.

## Methods and Analysis

### Study Design

The study is led by the Hematology Working Group within GMS. The study comprises 4 phases and includes a total of approximately 700 Swedish AML and ALL patients (Figure 1). The retrospective phase, involving WGS of tumor (90×) and normal (30×) samples from 150 adult AML patients and 100 pediatric ALL patients, has already been completed. Based on the retrospective data, we will assess technical feasibility and diagnostic efficiency of WGS to detect mandatory and highly recommended genetic variants in AML and ALL and determine to what extent WGS identifies additional clinically relevant genomic alterations not detected by SoC methods. The retrospective cohort was part of the SciLifeLab National Projects specifically focused on WGS, and therefore did not comprise WTS data. In the subsequent phases, we will complement with WTS to enable analysis of clinically relevant expressed fusion genes as well as explorative analysis of e.g., gene expression patterns and aberrant splicing (Supplementary Table 1).

**FIGURE 1 F1:**
[figure not shown]
Overview of the study phases, planned data generation, analysis, and reporting. Results from SoC diagnostics will be collected in parallel for all patients. T, tumor; N, normal; WGS, whole-genome sequencing; WTS, whole-transcriptome sequencing.

The prospective phase encompasses WGTS of prospectively collected samples from approximately 350 adult and pediatric ALL and AML patients (Figure 1). WGS will be performed for tumor (90×) and normal (30×) samples, and WTS (50 million read pairs) for tumor samples only. The choice of sequence depth is based on recent recommendations and data from a previous study including acute leukemia samples (4, 14, 15). Samples will be processed in parallel with SoC methods but without a strict time limit for analysis and interpretation. The duration of this phase will be approximately 12 months, starting in May 2021.

The real-time validation phase comprises WGTS of prospectively collected samples from approximately 100 ALL and AML patients, as described for the prospective phase (Figure 1). The aim is to perform WGTS and report the results within the required time frame for genetic diagnostics of acute leukemias in parallel with SoC methods. The duration of this phase will be 3–6 months.

During the follow-up phase, patient outcome data will be recorded for those included in the prospective and real-time validation phases. At least 2 years of follow-up after the last included patient will be required for meaningful health-economic analysis.

### Endpoints

Primary and secondary endpoints are listed in Table 1.

**TABLE 1 T1:** Primary and secondary endpoints.

Primary study endpoint (key phases)	Primary outcome measure
Diagnostic efficiency (retrospective and prospective phases)	Percentage of acute leukemia patients for whom all mandatory and highly recommended genetic variants found by SoC methods are also detected by WGTS*
Improved diagnostic yield (retrospective and prospective phases)	Percentage of acute leukemia patients for whom genetic variants relevant for classification or risk stratification are identified by WGTS* but not by SoC
**Secondary study endpoints (key phases)**	**Secondary outcome measure**
Technical feasibility (retrospective and prospective phases)	Percentage of patients for whom WGTS* analysis and interpretation is successful
Clinical feasibility for routine implementation (real-time validation phase)	Percentage of patients for whom WGTS analysis and interpretation is successful within a given time frame
Clinical utility (prospective and real-time validation phases)	Percentage of acute leukemia patients for whom patient management and/or therapy decision is/could be changed based on variants detected only by WGTS
Health-economic efficiency (all phases)	Micro-costing and cost effectiveness analysis of WGTS* compared to SoC

**For the retrospective phase, only WGS data are available.*

#### Primary Endpoints

##### Diagnostic Efficiency

Diagnostic efficiency is based on

(1)the percentage of patients for whom WGS detects (or excludes) all mandatory and highly recommended variants identified by cytogenetics, FISH, genomic arrays, NGS panels and/or multiplex ligation-dependent probe amplification (retrospective and prospective phases);(2)the percentage of patients for whom WTS detects all mandatory and highly recommended variants identified by RT-PCR or FISH (prospective phase); and(3)the percentage of patients for whom combined WGTS detects all mandatory and highly recommended variants identified by SoC diagnostics (prospective phase).

In the real-time validation phase, percentages for WGS and WGTS will be recorded separately for tumor-only analysis (after 2–3 weeks) and tumor-normal analysis (after 4 weeks or when a germline sample has been analyzed).

##### Improved Diagnostic Yield

Improved diagnostic yield is determined by the percentage of acute leukemia patients for whom genetic variants relevant for classification or risk stratification are identified by WGTS but not by SoC methods (prospective phase). This includes inconclusive cases by SoC and genetic variants that were missed by SoC technologies but also those that were not actively screened for with SoC. In the real-time validation phase, improved diagnostic yield will be recorded separately for tumor-only and tumor-normal analysis.

#### Secondary Endpoints

##### Technical and Clinical Feasibility

Technical feasibility is assessed by the percentage of patients for whom WGTS analysis and interpretation are successfully completed without a strict time limit (prospective phase). Here we will also measure the percentage of samples where SoC tests or WGTS analysis were uninformative for mandatory and highly recommended variants.

Clinical feasibility is tested during the real-time validation phase and refers to the percentage of patients for whom WGTS analysis is successfully reported within the required time frame for genetic diagnosis of acute leukemias (i.e., 2 weeks for pediatric acute leukemias and 3 weeks for adult acute leukemias). Of note, this does not include targeted molecular tests that need to be performed in AML within the first days after diagnosis to decide on targeted therapy (e.g., *PML:RARA*, *FLT3*-ITD).

##### Clinical Utility

Clinical utility is measured by the percentage of patients for whom patient management or therapy decisions (according to national care programs and/or clinical trial protocols) are/potentially could be changed based on variants detected by WGTS, but not SoC diagnostics. Specifically, the percentage of patients for whom WGTS findings lead to targeted treatment options and/or a change in treatment options not identified by SoC will be recorded. This information will be retrieved from registries and retrospective analysis of medical records (prospective and real-time validation phases).

##### Health-Economic Evaluation

The health-economic evaluation consists of two analytic parts:

(1)A micro-costing analysis which is performed to estimate and compare the average cost of SoC and WGTS.(2)Analysis of cost-effectiveness of WGTS (defined further below) in comparison with SoC will be estimated using economic simulation modeling.

### Participating Sites

The seven Swedish sites (Gothenburg, Linköping, Lund, Stockholm, Umeå, Uppsala, and Örebro) belonging to the Clinical Genomics Platform at SciLifeLab and corresponding Genomic Medicine Centers (GMCs) will participate in the study. While patients with acute leukemia will be recruited at all sites, sample processing, sequencing, and data analysis will be performed centrally at select locations (Supplementary Table 2).

### Study Population

#### Population and Sample Size

The retrospective cohort includes samples from 150 AML patients and 100 ALL patients for whom WGS has already been performed. For the prospective and real-time validation phases, the aim is to include a total of 450 consecutive adult and pediatric patients with a confirmed diagnosis of ALL or AML from any of the participating sites. This number corresponds approximately to the number of patients diagnosed with acute leukemias on average in Sweden within one year. The study will end after 15-18 months (depending on the patient recruitment rate) when the sample size has reached 450. The estimate of sample size at each site, based on the average number of patients diagnosed per year, is shown in Supplementary Table 3.

#### Inclusion Criteria (the Prospective and the Real-Time Validation Phases)

All patients diagnosed with acute leukemia and analyzed with genetic SoC methods will be offered inclusion. Patients will be included if the patient/guardians provide informed written consent and as long as sufficient tumor material is available for SoC tests and WGS.

### Sample Preparation

A bone marrow sample will be used for chromosome banding and FISH analyses. From the same sample, DNA and RNA will be extracted using standard procedures at each participating site. In the event of limited material from a bone marrow sample, peripheral blood may be used. The expected tumor purity in bone marrow as well as peripheral blood samples is >80–90%. WGTS of leukemic samples will be performed using surplus DNA and RNA that remain after SoC tests in most cases, without requiring additional sampling.

As germline material, a skin biopsy will be collected from which fibroblasts are cultured and DNA prepared. Alternatively, T-cells are isolated (adult AML) or a remission sample (taken at day 29) is used (adult ALL) as an alternative source of germline DNA. If a patient does not achieve remission, germline DNA will be extracted from a buccal swab sample also collected at day 29.

### SoC Genetic Diagnosis

The SoC methods used in AML include chromosome banding analysis to identify numerical and structural chromosomal aberrations, targeted FISH analysis to investigate stratifying structural variants, targeted NGS panel [e.g., GMS Myeloid custom panel (Twist Bioscience, South San Francisco, CA, United States) or Archer VariantPlex Myeloid panel (ArcherDx, Boulder, CO, United States)] and fragment analysis for selected mutations. Some of the fusion genes detected by FISH can alternatively be detected by RT-PCR. Supplementary Table 1 shows which types of genetic alterations are typically detected with which method.

The SoC methods used in ALL includes chromosome banding analysis, FISH to identify fusion genes and/or genomic arrays to identify CNAs. For pediatric patients and young adults with ALL, multiplex ligation-dependent probe amplification may also be performed to detect CNAs.

The methods included in SoC at each site are listed in Supplementary Tables 5–9. Since SoC is determined by national care programs and/or clinical study protocols, each site will analyze the same set of genetic alterations. As an example, mandatory genetic variants that must be detected or excluded in adult AML, according to current treatment protocols/guidelines, as well as highly recommended recurrent genetic variants are listed in Supplementary Table 4 (16).

### WGTS Protocol

All samples, regardless of tumor content, will be analyzed. WGS libraries will be prepared with the TruSeq PCR-Free kit (Illumina, San Diego, CA, United States). WTS libraries will be prepared with the TruSeq Stranded mRNA kit or Illumina Stranded mRNA Prep (Illumina). Input requirements are 1200 ng DNA at a concentration of 25 ng/μl and 500 ng RNA at a concentration of 10 ng/μl (RIN value ≥ 7). If sufficient material is unavailable, individual sequencing centers may use alternative PCR-free methods with lower input requirements. Sequencing will be performed using the NovaSeq platform (Illumina) with paired-end 150 bp read length. For WGS, leukemia samples will be sequenced to a target of 90× coverage and the matched germline samples to 30× coverage. For WTS, we aim to generate 50 million read-pairs or more for each leukemia sample.

### Bioinformatic Analysis

Bioinformatic analysis of WGTS data will be performed at each sequencing site. The bioinformatic pipelines at each site are outlined in Supplementary Table 10. Further development and optimization will be performed continuously throughout the study. Code will be made available in public repositories (Supplementary Table 10). GRCh38 will be used as the reference genome at all sites. In parallel, all sequencing data will be analyzed with the Illumina best practice workflow DRAGEN. This analysis will be performed in Stockholm and Lund; raw sequencing data generated at other sites will be transferred to either Stockholm or Lund for analysis (Supplementary Table 2).

### Data Interpretation

In all phases, data analysis and interpretation will be performed in two steps:

1.Targeted analysis of genes/variants that are mandatory to include or exclude in SoC. The lists of mandatory genetic variants for AML (Supplementary Table 4) and ALL were prepared based on the WHO classification (1) and current clinical study protocols and national/European guidelines.2.Targeted analysis of an extended list of highly recommended genes/variants that is curated 1–2 times per year by the GMS Hematology Working Group. This list includes additional variants that are determined to be clinically relevant based on literature and other classifications (Supplementary Table 4).

In the retrospective phase, matched tumor-normal WGS data will be analyzed to identify mandatory and highly recommended genetic variants in AML (Supplementary Table 4) and ALL, while the prospective phase also includes tumor WTS data.

In the real-time validation phase, tumor-only analysis and interpretation will be performed according to step 1 within 2 weeks for pediatric acute leukemias and 3 weeks for adult acute leukemias, followed by tumor-normal analysis and final interpretation according to step 2 within 4 weeks (except for adult ALL where the remission sample will be collected at day 29).

After the completion of patient recruitment, a retrospective explorative research analysis of the entire WGS and WTS datasets will be performed to identify novel genomic aberrations of clinical interest.

### Reporting

For the whole study duration SoC will be the primary data source for subtype classification and the study data will be regarded as complementary information. Genetic variants of diagnostic, prognostic, and/or predictive impact detected by WGTS will be interpreted and recorded according to the standard procedure at each participating center.

In the real-time validation phase, all mandatory variants detected by WGTS will be included in the first clinical report [after 2 (ALL) or 3 (AML) weeks], whereas highly recommended variants will be included the final clinical report (after 4 weeks), and may potentially influence classification/risk stratification and treatment.

In the prospective phase, clinically relevant variants that are detected by WGTS, but not by SoC, will be reported to the hematologist/pediatric oncologist as a complementary clinical report after being verified with another clinically validated method (e.g., FISH, PCR or NGS-based gene panels). Thus, also in this phase, such variants may influence risk classification and treatment.

### WGTS Study Report

During the prospective and real time validation phases, we will prepare a WGTS study report for each patient with the following information:

•Availability of materials for SoC and WGTS.•Sequencing metrics (sequence depth, sequence coverage, and other QC data).•Mandatory and highly recommended variants identified by both SoC and WGTS.•Mandatory and highly recommended variants that are identified by WGTS but not SoC, and if available results of verification experiments.•Mandatory and highly recommended variants that are identified by SoC but not WGTS, and if available results of verification experiments.•Potential impact of WGTS findings on classification, risk stratification and therapy selection.•For the real-time validation phase, turnaround time in calendar days from sample collection to first clinical report (based on tumor-only analysis) and to the final report (tumor/normal analysis).

During the real-time validation phase, in addition to a WGTS study report, we will include WGTS findings in the clinical report according to the standard clinical reporting practice. Also, national review meetings, including physicians, clinical scientists, and bioinformaticians will be held on a regular basis to discuss the findings and their clinical interpretation (in particular, if WGTS detects clinically relevant genomic variants not identified by SoC or if WGTS and SoC show conflicting results) and to harmonize the reports between sites.

We have also prepared standardized templates for collection of metadata (e.g., sample data, sequencing protocol, sequencing platform, genome version, software and parameters used for variant calling, annotation and interpretation, etc.) to ensure that all sites collect the same information.

### Health-Economics Analysis

The micro-costing analysis will be performed initially at two sites and ultimately at all four sites where WGTS is carried out (Gothenburg, Lund, Stockholm, and Uppsala). A generic micro-costing spreadsheet will be developed and applied to Swedish genetic laboratories estimating the average cost of SoC and WGTS. The micro-costing will capture the economic burden to each laboratory; including the costs of personnel, equipment/material, bioinformatic analysis and interpretation, storage and compute costs, test consumables as well as platforms used (for WGTS) and potentially iterative testing. An activity-based costing model will be applied to calculate the total cost of the included diagnostic techniques. The analysis will take into account that some rapid conventional testing will be required in parallel to WGTS.

Cost-effectiveness of WGTS in comparison with SoC will be estimated using economic simulation modeling where the value of WGTS in quality adjusted life years is driven by the proportion of patients for whom management or therapy decision is/could be changed based on variants detected by WGTS, but not by SoC diagnostics. The outcome of patients where WGTS led to changes in risk stratification will be compared to the outcome of patients in risk groups defined by SoC only.

Based on literature, study outcomes (i.e., improved diagnostic yield and clinical utility), and registry data (e.g., the Swedish Blood Cancer Register, the National Patient Register, and the Swedish Prescribed Drug Register from the National Board of Health and Welfare), a simulation model will be built to estimate the diagnostic and the long-term cost for AML and ALL patients. The model will also be able to estimate the long-term health outcomes and the incremental cost effectiveness ratio of WGTS vs. SoC.

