Currently, there is a debate regarding the appropriate sequencing depth as well as whether normal sample should be included in the WGS analysis. Yet, current consensus for correct somatic variant calling by WGS are read depths of 90–100× for tumor samples and 30× for the normal control (15). For clear and reliable distinction between germline and somatic variants, comparative analysis of matched tumor and normal samples is also considered imperative (15). Based on the improved diagnostic yield reported by the study of Duncavage et al. that performed tumor-only analysis with WGS at 60× target coverage, our tumor-normal analysis using WGS at 90× coverage is expected to demonstrate a higher diagnostic performance. Our findings will also help address the current lack of standardized sequencing parameters and metrics for WGS. Furthermore, with the notable advantages of WTS such as oncogenic gene fusion detection and improved disease subclassification (6), additional diagnostic value gained by integration of WTS to WGS will be assessed in our study.

In the study by Duncavage et al., the cost of a WGS-based diagnostic approach was estimated to be $1,300–$1,900 (13). However, since the authors of this study performed lower depth of sequencing (60×) than what is currently recommended (15), the actual price could be higher and prohibitive for a realistic application of such sequencing methods in routine practice. They also used their in-house bioinformatics tools which does not take into account instrumentation and licensing fees by commercial solutions. These factors together likely caused underestimation of the total cost. Indeed, in a separate study, the cost of tumor-normal WGS (90× tumor coverage and 30× reference coverage) was determined to be >$3,000 (23). Additionally, the cost of WGS-based diagnostics may be higher at smaller clinical centers compared with larger institutions; in the former clinical setting where fewer patients are received, batching many patient samples to save cost is undesirable in the interest of reasonable/expected turn-around-time. Following the recommended sequencing strategy and using the matched tumor-normal samples (15), we aim to provide a more realistic estimation of the WGS/WTS-based diagnostic test.

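### The laboratory-only costing boundary does not cover clinic-side collection of the germline sample, a cost the article describes only for WGTS

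*Protocol article*

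**What the plan says.** All references are to the protocol article.

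- **Health-Economics Analysis, boundary.** "The micro-costing will capture the economic burden to each laboratory".
- **Health-Economics Analysis, components.** The items are introduced as "including the costs of personnel, equipment/material, bioinformatic analysis and interpretation, storage and compute costs, test consumables as well as platforms used (for WGTS"), followed by possible repeat testing. The total is defined by technique: "An activity-based costing model will be applied to calculate the total cost of the included diagnostic techniques". The section adds that rapid conventional tests still needed alongside WGTS will be taken into account.
- **Health-Economics Analysis, model.** The simulation model draws on literature, study outcomes and national registers. It is to estimate diagnostic and long-term costs and an incremental cost-effectiveness ratio. The micro-costing is not named among its inputs. Under Secondary Endpoints, micro-costing and cost-effectiveness are listed as two parts of one evaluation.
- **Sample Preparation, germline sources.** The first-named source is a biopsy: "As germline material, a skin biopsy will be collected from which fibroblasts are cultured and DNA prepared". Then: "Alternatively, T-cells are isolated (adult AML) or a remission sample (taken at day 29) is used (adult ALL"). For patients without remission, "germline DNA will be extracted from a buccal swab sample also collected at day 29". The remark that extra sampling is usually unnecessary concerns leukemic samples only.
- **SoC Genetic Diagnosis.** The methods listed for AML and ALL are banding, FISH, arrays, targeted panels, fragment analysis, RT-PCR and probe amplification. None is described as using a germline sample.
- **Discussion.** Matched tumor-normal analysis is reported as considered imperative. Using such samples, "we aim to provide a more realistic estimation of the WGS/WTS-based diagnostic test".

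**The concern.** A narrow costing perspective does little harm when the costs it drops fall equally on both strategies, because they cancel in the difference. Here the cost left outside the boundary belongs to one strategy. The tumor-normal workflow needs a second specimen, and obtaining it is work for a clinic. A spreadsheet built to the stated boundary would count the 30× sequencing of the normal sample but not the procedure that produced it.

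At stake is the health-economic secondary endpoint, which feeds the study's wider question of whether WGTS can replace SoC testing. The Discussion also rests its promise of a more realistic cost on the use of matched normal samples, so the cost of obtaining them matters to that promise.

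**Working it through.** The article states no collection cost, cost difference or cost-effectiveness ratio, so there is no figure to reproduce. The check has three steps: sort the germline work by the stated boundary, establish the direction of the error, and show what size it could take on assumed inputs.

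**1. What falls inside and outside the boundary**

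| Step | Done by | Inside the laboratory boundary? |
|---|---|---|
| Skin biopsy | clinic | no |
| Buccal swab at day 29 | clinic | no |
| Extra draw for T-cells or day-29 remission sample, if beyond usual care | clinic | no (need for an extra draw not stated) |
| Fibroblast culture, T-cell isolation, DNA preparation | laboratory | yes (personnel, material, consumables) |
| 30× sequencing and analysis of the normal sample | laboratory | yes |

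Only the act of collection is uncovered. On the SoC side no germline collection is described, so there is nothing to offset it.

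**2. Direction**

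Let c be the clinic-side collection cost, f the share of patients who need a collection beyond usual care, and D the laboratory-only cost difference, WGTS minus SoC.

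- Cost omitted per patient = c × f
- Full difference = D + c × f

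Because c and f cannot be negative, the laboratory-only difference is never too high. Any error favours WGTS.

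**3. Size on assumed inputs**

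The only benchmark in the article is more than $3,000 for tumor-normal WGS at 90×/30× (Discussion). The values of c, f and D below are assumptions. For positive D, the understatement as a share of the full difference is c × f / (D + c × f).

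| c | f | c × f | Share of $3,000 | D = $500 | D = $1,500 | D = $3,000 |
|---|---|---|---|---|---|---|
| $50 | 25% | $12.50 | 0.4% | 2.4% | 0.8% | 0.4% |
| $200 | 50% | $100 | 3.3% | 16.7% | 6.25% | 3.2% |
| $500 | 100% | $500 | 16.7% | 50.0% | 25.0% | 14.3% |

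For example, the last row gives 500/3,000 = 16.7%, 500/(500 + 500) = 50.0%, 500/(1,500 + 500) = 25.0% and 500/(3,000 + 500) = 14.3%. The $3,000 is a floor and covers WGS without WTS, so the shares of test cost are upper values for each assumed c and f. The effect is large only if D is small and most patients need a separate procedure.

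**4. Carry-over to the ratio**

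If the laboratory-only figure supplies the model's diagnostic cost, the numerator of the ratio is too low by c × f. With a positive QALY gain, the ratio is too low by c × f divided by that gain. The percentages above do not transfer, because the numerator also holds any difference in long-term costs. They would transfer only if long-term costs were equal under both strategies.

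**The case against.** The strongest reply is that the omission is inferred. The component list is open-ended, the spreadsheet is still to be developed, and an article leaves item-level costs to a fuller document. That is fair as far as the list goes, but the boundary itself is stated. Any item added later would still have to be a burden on the laboratory, and a biopsy in a clinic is not.

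It can also be said that the authors plan to count at least one added cost of the WGTS strategy, namely the rapid conventional tests run alongside it. This shows that they are not disregarding such costs, but it does not bring collection inside the boundary. Likewise, the Discussion faults an earlier estimate for sequencing depth, instrumentation and licensing fees, not for specimen collection, so the article does not break a promise it made about sampling.

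Three stronger readings are tempting and are not supported:

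- **That all germline work is left uncosted.** Culture, cell isolation, DNA preparation and sequencing are laboratory work and fit the listed components.
- **That verification of WGTS-only variants is another omitted cost.** The Reporting section has such variants reported in the prospective phase "after being verified with another clinically validated method (e.g., FISH, PCR or NGS-based gene panels"). These are laboratory tests and lie inside the boundary. The section states this requirement only for the prospective phase, so it may be a study safeguard. Charging it to routine WGTS could overstate the cost.
- **That the ratio is known to mix a laboratory perspective with a health-care one.** The article does not say that the micro-costing is the model's only diagnostic cost. The model could take collection costs from literature or registers. Registers alone are unlikely to settle it, though: patients have WGTS in parallel with SoC, so a recorded biopsy would reach the WGTS side only under an explicit rule, and none is given.

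**Conclusion.** The point holds in a limited form. The stated boundary does not cover clinic-side germline collection, the article describes that collection only for WGTS, and the resulting error in the diagnostic cost difference can only favour WGTS.

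The documents do not allow the size to be determined. On the assumed inputs it runs from under 1% to 50% of the cost difference, and it may well be at the low end: the article does not say how many patients have a biopsy, or whether the T-cell and remission sources add any procedure to usual care. Bias in the cost-effectiveness ratio follows only if the laboratory figure is carried into the model, which is plausible but unstated.

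This is a cheap improvement to one part of a secondary endpoint. It does not touch the primary endpoints, and it does not show that the health-economic conclusion will be wrong.

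**What to change.** In the Health-Economics Analysis section:

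1. Add clinic-side germline collection to the WGTS side of the costing: skin biopsy, buccal swab, and any draw beyond usual care. Use unit costs for each, weighted by the observed share of patients needing each source.
2. State that this total is the diagnostic cost used in the cost-effectiveness model.
3. Report the laboratory-only total as a secondary result.

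Culture, T-cell isolation and DNA preparation need no new item beyond the laboratory costing. Verification tests should not be added automatically to the routine WGTS cost.

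The price is a few extra spreadsheet rows, the unit costs to fill them, and a slightly less favourable cost for WGTS.
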